##### Stage-2 Monitoring

Participants categorized as stage-2 T1D (positive autoantibodies with dysglycemia) will have more frequent clinic visits every 3 months for HbA_1c_ and glucose testing. An OGTT or CGM will be performed annually or sooner if there is a 10% or more rise in HbA_1c_ from baseline.

##### Monitoring for Single Autoantibody Results

Participants with a single autoantibody undergo metabolic assessment only if symptoms develop. For children younger than the age of 6 years, autoantibody screening will be repeated within 6 months for confirmation, then annually throughout the study. For children aged 6 years or older, annual screening will be conducted for the duration of the study. Autoantibody monitoring will be discontinued if a participant seroconverts to a negative status. No physician visits are required, and families are encouraged to contact the research team if T1D symptoms arise in the future.

##### Monitoring for Participants With Negative Autoantibodies

All participants who test negative for autoantibodies will undergo follow-up autoantibody testing at the conclusion of the 5-year study period.

#### Other Monitoring Measures

##### Clinical Measurements

Weight, height, and BMI are assessed annually for participants with positive autoantibodies.

##### Psychological Assessment

Parents of children with positive autoantibody results will undergo psychological assessment within one week of receiving screening results. Assessments are repeated during follow-up at 6 and 12 months to track changes over time.

### Outcome Definitions and Metrics

#### Feasibility Metrics

The feasibility of the screening program will be evaluated using the following key metrics.

Recruitment rates: The proportion of eligible participants successfully recruited into the study.Screening refusal rates: The percentage of eligible participants who decline participation.Completed screening visit rates: The percentage of participants completing the initial screening visit (phase 1).Completed counseling visit rates: The percentage of participants with positive autoantibody results who complete the counseling session and educational curriculum (phase 2).Completion of long-term follow-up: The percentage of participants with presymptomatic T1D who complete their monitoring visits during the 4-year follow-up period (phase 3). Participants progressing to clinical T1D before the study conclusion will transition to standard clinical care and be considered as having completed follow-up.

#### Prevalence of Presymptomatic T1D at Screening

Metabolic staging performed during the screening results visit (phase 2) will classify participants into the following stages.

Stage-1 T1D: Presence of two or more islet autoantibodies with normal glycemia. Criteria include HbA_1c_ <5.7%, fasting blood glucose <100 mg/dL, and a 2-hour OGTT <140 mg/dL. For CGM users, values >140 mg/dL should be less than 10% of the time over 10 days of continuous wear.Stage-2 T1D: Presence of two or more islet autoantibodies with dysglycemia. Criteria include HbA_1c_ between 5.7% and 6.4%, fasting blood glucose between 100-125 mg/dL, and a 2-hour OGTT between 140-199 mg/dL. For CGM users, values more than 140 mg/dL should be between 10% to less than 20% of the time over 10 days of continuous wear.Stage-3 T1D: Clinical onset of T1D marked by one or more islet autoantibodies and hyperglycemia. Criteria include HbA_1c_ 6.5%, fasting blood glucose levels 126 mg/dL, and a 2-hour OGTT 200 mg/dL. For CGM users, values >140 mg/dL must occur at least 20% of the time over 10 days of continuous wear.At risk (pre–stage-1 T1D): Defined as the presence of a single islet autoantibody with normal glycemia.Isolated genetic predisposition: Defined as the presence of positive genetic risk markers without accompanying islet autoantibodies.

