#### Intervention: T1D Screening

##### Islet Autoantibodies Screening

The program uses antibody detection by agglutination–polymerase chain reaction (ADAP) assay, a cutting-edge technology developed by Enable Biosciences. The assay measures islet autoantibodies [23-27], including insulin autoantibodies, glutamic acid decarboxylase autoantibodies, IA-2 autoantibodies, and zinc transporter 8 autoantibodies, using dried blood spots on filter paper. The ADAP assay offers notable advantages over other assays for large-scale analysis, such as cost-effectiveness, high sensitivity and specificity, and minimal sample volume requirements. These features make it suitable for large-scale applications, including home testing [25-27].

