### Statistical Analyses

#### Sample Size

The target enrollment is 1300 participants (or 322 families), based on the feasibility of recruiting 70% of eligible families from the UDC clinic cohort. The estimated seropositivity rate for islet autoantibodies among children with an FDR diagnosed with T1D is estimated at 5% to 15%, with a 90% significance level and 80% power. Considering that the UDC serves approximately 450-500 children with T1D, and that the typical Saudi family has 4-6 children younger than the age of 18 years, this sample size is calculated to be sufficient. Recruitment will be expanded to FDRs outside the UDC cohort if the family target is met without reaching the participant’s goal.

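### The at-risk category and its progression rate rest on one unconfirmed four-antibody result, although a repeat is already scheduled for every single-antibody child

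*Protocol article*

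**What the plan says.** All references are to the protocol article.

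- **Category.** Prevalence of Presymptomatic T1D at Screening fixes the timing: "Metabolic staging performed during the screening results visit (phase 2) will classify participants into the following stages". The at-risk (pre–stage 1) category is "Defined as the presence of a single islet autoantibody with normal glycemia". No second sample is required.
- **Assay.** Islet Autoantibodies Screening lists four targets, "including insulin autoantibodies, glutamic acid decarboxylase autoantibodies, IA-2 autoantibodies, and zinc transporter 8 autoantibodies, using dried blood spots on filter paper". Performance is given in words only: "high sensitivity and specificity".
- **Status of a single positive.** Participants With Equivocal Results covers the single-antibody child; the section on positive results is kept for multiple antibodies.
- **Repeats.** Monitoring for Single Autoantibody Results states: "For children younger than the age of 6 years, autoantibody screening will be repeated within 6 months for confirmation, then annually throughout the study". From age 6 the test is repeated yearly and is not called confirmation. A child who turns negative leaves antibody monitoring. Nothing says that the category or the reported proportion changes.
- **Progression.** T1D Progression Rate reports the annual rate to stage 3 by initial stage. Monitoring for Disease Progression puts single-antibody children into the four-year follow-up.
- **Planning figure.** Sample Size says that seropositivity "is estimated at 5% to 15%, with a 90% significance level and 80% power", with 1300 children as the target.

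**The concern.** The clinical sections treat one positive antibody as provisional, while the outcome definition treats it as final. With four antibodies and any one sufficing, the chances of error add up, and nearly all the resulting false positives land in the single-antibody group.

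Two reported quantities are exposed. The at-risk proportion would be too high. The progression rate of the at-risk stratum would be too low, because children without autoimmunity sit in its denominator. The pilot is meant to inform a national programme, for which the yield and false-positive burden of single-antibody results matter. The data that would reveal the problem are already being collected.

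**Working it through.** **Inputs.** From the article: four antibodies, 1300 children, expected seropositivity 5% to 15%. Assumed, because the article gives no figure: specificity *s* per antibody of 98% to 99.9%, errors independent between antibodies, sensitivity 1.

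**The article's own figure.** It has no false-positive figure to reproduce. The target of 1300 is compatible with its feasibility basis: 70% of 450–500 is 315–350 families, which contains 322, and 322 × 4 = 1288. Expected seropositives are 0.05 × 1300 = 65 to 0.15 × 1300 = 195.

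**Step 1: false positives among unaffected children.**
P(exactly one) = 4(1 − s)s³. P(two or more) = 1 − s⁴ − 4(1 − s)s³.

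| s | P(exactly one) | per 1300 | P(two or more) | per 1300 |
|---|---|---|---|---|
| 98% | 7.53% | 98 | 0.234% | 3.0 |
| 99% | 3.88% | 50 | 0.059% | 0.8 |
| 99.5% | 1.97% | 26 | 0.015% | 0.2 |
| 99.9% | 0.40% | 5 | 0.0006% | 0.01 |

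**Step 2: false share of all observed seropositives.** With f = 1 − s⁴ and observed seropositivity P, the number of false positives is 1300(1 − P)f/(1 − f). For example, s = 99% and P = 10% give 1170 × 0.0394/0.9606 = 48, and 48/130 = 37%.

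| s | P = 5% (65) | P = 10% (130) | P = 15% (195) |
|---|---|---|---|
| 98% | impossible (f = 7.8% exceeds 5%) | 98 (76%) | 93 (48%) |
| 99% | 51 (78%) | 48 (37%) | 45 (23%) |
| 99.5% | 25 (38%) | 24 (18%) | 22 (11%) |
| 99.9% | 5 (8%) | 5 (4%) | 4 (2%) |

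**Step 3: false share within the at-risk group.** Assume further that half to two thirds of the 130 positives at P = 10% carry a single antibody, that is 65 to 87 children. Expected false single positives are 47.3, 23.5 and 4.7 at 99%, 99.5% and 99.9%. The false share is then about 55–73%, 27–36% and 5–7%.

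**Step 4: dilution of the progression rate.** If false positives hardly progress, the observed at-risk rate is roughly the true rate times (1 − false share). That is 27–45%, 64–73% and 93–95% of the true rate in the three cases.

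**Step 5: what a repeat could remove.** Suppose the same antibody must be positive again and errors are independent between samples. At a true seropositivity of 10%, false single positives fall from 88 to 1.8 (98%), 45 to 0.5 (99%) and 23 to 0.1 (99.5%). This is a best case, since persistent cross-reactivity would survive the repeat.

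**The case against.** **The size is assumed.** This stands. The count moves about twentyfold, from 5 to 98 children, over a range that the article does not narrow. A reader might infer that the bias can match the whole 5–15% range. It cannot: only the 98% case reaches the lower end and none reaches 15%.

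**The primary result is safe.** This also stands. Primary Objectives names stages 1, 2 and 3. Stages 1 and 2 need two antibodies, and stage 3 needs hyperglycemia as well as an antibody. A reader might infer that the primary prevalence, or a reported overall seropositivity, is biased. The first is hardly touched, and the second appears only as a planning figure.

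**A first-sample count is what a section headed 'at Screening' promises, and the repeats have a use.** Partly right. Repeats are acted on at every age, because a negative result ends antibody monitoring, so it would be wrong to call them ignored. They are simply not used in the category or the rate, and the at-risk label carries no mark that it is unconfirmed.

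**The progression harm is narrow.** Right. The Kaplan-Meier analysis is for presymptomatic participants, defined elsewhere as stage 1 or 2. Only the separate at-risk stratum of the annual rate is exposed, and only if testing positive there includes single-antibody children. The follow-up section supports that reading; the results-disclosure sections point the other way.

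**Cost per case is not shown to be biased.** Right. A reader might infer that single positives flatter it, but Statistical Analysis does not say that they count as cases. The term is open.

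**Confirmation can mislead.** Right, and it shapes the fix. A negative repeat may be true reversion. Selecting children by a later test while counting time from screening would build in event-free time and lose early progressors.

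**This belongs in a fuller document.** Not persuasive here: the article itself states the category and the initial-stage rule, and these sit badly with its own handling of the result.

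**Conclusion.** The point holds for the at-risk category and, where single-antibody children are included, for that stratum's progression rate. Both rest on one unconfirmed result that the article elsewhere treats as equivocal. With independent errors and an assumed per-antibody specificity of 99% to 99.5%, about 26 to 50 of 1300 unaffected children would be false single positives, which is material against 65 to 195 expected seropositives. At 99.9% it is about 5, and the issue is minor. The article does not allow a choice between these cases. False multiple positives number about 3 at 98% and fewer than 1 from 99% upwards, so the primary prevalences are not in question. The change should be made, but it concerns reporting and does not challenge the main result.

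**What to change.** 1. Label the first-sample figure as single positive at screening (unconfirmed), and state the assay specificity relied on.
2. Once the first repeat already scheduled for single-antibody children is in, report separately the proportions confirmed, negative, progressed to multiple antibodies and not retested. Give them by age group with the repeat interval stated, because the interval is up to 6 months under age 6 and about a year from age 6. Say whether confirmation means the same antibody.
3. Describe a negative repeat as not confirmed, without calling it either a false positive or seroconversion.
4. Keep the progression rate by initial stage. Add an at-risk rate for confirmed single positives with time counted from the confirming sample (a landmark), and report events before the repeat separately.
5. State that single positives are not counted in cost per case detected, or show that figure with and without confirmed single positives.

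This changes wording and analysis only, with no new sample or visit. The confirmed figure comes up to a year later. Screening runs from May 2024 to April 2025, so first annual repeats fall from about May 2025 to April 2026, for many children after the mid-2025 screening analysis. It also depends on attendance at the repeat, which is why the proportion not retested must be shown.

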#### Incidence of DKA

The incidence of DKA at the clinical onset of T1D will be tracked during the long-term follow-up phase (phase 3). DKA occurrences will be captured from clinical records and follow-up visits.

#### T1D Progression Rate

The annual progression rate to stage-3 T1D will be tracked in participants testing positive during the follow-up phase (phase 3) and categorized based on their initial stage.

#### Effectiveness of Educational Interventions

The effectiveness of the educational curriculum will be evaluated using pre- and postintervention tests completed by caregivers. These tests are developed to measure changes in knowledge related to the curriculum’s objectives, providing a comprehensive assessment of the intervention's effectiveness in preparing caregivers for presymptomatic T1D management.

#### Health Care Resource Use for Cost-Effectiveness Analysis

Health care resource use will include both program-related and external health care resources. Program-related costs will encompass autoantibody testing, metabolic profiling, results notification visits, and educational or follow-up visits. Non–program-related costs will include diabetes clinic visits (eg, consultations with physicians, educators, nutritionists, or psychologists), emergency department visits for diabetes or DKA, hospitalizations for diabetes, laboratory and imaging studies, and prescription medications for diabetes management either inpatient or outpatient.

### Statistical Analyses

#### Sample Size

The target enrollment is 1300 participants (or 322 families), based on the feasibility of recruiting 70% of eligible families from the UDC clinic cohort. The estimated seropositivity rate for islet autoantibodies among children with an FDR diagnosed with T1D is estimated at 5% to 15%, with a 90% significance level and 80% power. Considering that the UDC serves approximately 450-500 children with T1D, and that the typical Saudi family has 4-6 children younger than the age of 18 years, this sample size is calculated to be sufficient. Recruitment will be expanded to FDRs outside the UDC cohort if the family target is met without reaching the participant’s goal.

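### The significance and power clause behind the target of 1300 has no defined meaning and does not yield 1300; the target rests on feasibility and should be supported by a precision statement

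*Protocol article*

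**What the plan says.** The Sample Size section opens with the target and its basis: "The target enrollment is 1300 participants (or 322 families), based on the feasibility of recruiting 70% of eligible families" of the clinic cohort. It then gives the expected rate of seropositivity as "estimated at 5% to 15%, with a 90% significance level and 80% power". After citing 450-500 children with T1D at the clinic, it closes the argument with "the typical Saudi family has 4-6 children younger than the age of 18 years, this sample size is calculated to be sufficient". A last sentence allows recruitment of relatives from outside the clinic cohort if the family target is reached before the participant target.

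Two other places matter. Under Primary Objectives, prevalence of stages 1, 2 and 3 is something to be determined, with no comparison. Under Statistical Analysis, feasibility metrics and stages are to be reported as percentages. No test of seropositivity or of stage prevalence is planned.

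**The concern.** The clause "90% significance level and 80% power" reads as the output of a formal calculation, and the section then calls the size sufficient. A power statement needs a null value, an alternative and an error rate. Here the only rates are the two ends of a planning range for one proportion, and the error rate as written is 0.90. If 90% confidence was meant, the calculation is one of precision and power has no part in it.

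At stake is what a reader may conclude about a primary outcome. The section says that the size has been shown to be enough, but gives no criterion for enough, neither a difference to detect nor a confidence interval width. The reader is offered a property that the design does not have, and is not told the one that it does have: how closely 1300 children will estimate the prevalence.

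**Working it through.** **Inputs from the Sample Size section.** N = 1300; 322 families; 70% of eligible families; 450-500 children with T1D at the clinic; 4-6 children per family; seropositivity 5% to 15%; 90%; 80% power. Sidedness, null value, alternative and margin are not stated.

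**1. The feasibility route, which is the stated basis.**
- 0.70 × 450 = 315 and 0.70 × 500 = 350 families. 322 lies in this range and equals 0.70 × 460.
- 322 × 4 = 1288, and 1300 / 322 = 4.04 children per family.

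This reproduces the target to within rounding, at the low end of 4-6 children.

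**2. The clause read literally (alpha = 0.90).** For 5% v 15% with 80% power, the one-sample and two-sample formulas give between 1 and 17 per group without continuity correction. Power would also be below the significance level, so this cannot be what was meant.

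**3. The clause read as alpha = 0.10 and a test of 5% v 15%.**
- One sample, two-sided: n = [(1.645 × √(0.05 × 0.95) + 0.842 × √(0.15 × 0.85)) / 0.10]² = [(0.3585 + 0.3005) / 0.10]² = 43.4, so 44. With 15% as the null value, 60.
- Two groups, two-sided: n = [(1.645 × √(2 × 0.10 × 0.90) + 0.842 × √(0.0475 + 0.1275)) / 0.10]² = [(0.698 + 0.352) / 0.10]² = 110.2, so 111 per group (130 with continuity correction).
- At n = 1300 the one-sample test has power of about 100%, not 80%.

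**4. The clause read as 90% confidence, with an assumed margin d.** n = 1.645² × p(1 − p) / d².
- p = 0.05, d = 0.01: 2.706 × 0.0475 / 0.0001 = about 1285.
- p = 0.15, d = 0.01: 2.706 × 0.1275 / 0.0001 = about 3450.

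The first is close to 1300, but it uses no power, the margin is not in the document, and it fails at the upper end of the plan's own range.

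**5. A hybrid formula with both terms, again with assumed margins.** n = (1.645 + 0.842)² × p(1 − p) / d².
- p = 0.05, d = 0.015: 1306.
- p = 0.15, d = 0.025: 1262.

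Several different invented margins land near 1300, so the stated inputs do not identify it.

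**6. What 1300 does deliver.** The 95% half-width for independent children is 1.96 × √(p(1 − p) / 1300). For siblings in families of equal size, multiply by √DE, where DE = 1 + (4.04 − 1) × ICC. The ICC is an assumption, as the document gives none. ICC 0.1 gives DE = 1.30, and ICC 0.2 gives DE = 1.61.

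| Seropositivity | Independent | ICC 0.1 | ICC 0.2 |
|---|---|---|---|
| 5% | 1.18 points | 1.35 | 1.50 |
| 10% | 1.63 points | 1.86 | 2.07 |
| 15% | 1.94 points | 2.22 | 2.46 |

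**The case against.** The strongest reply is that 1300 never depended on the clause. The section's first sentence says that the target is "based on the feasibility of recruiting 70% of eligible families from the UDC clinic cohort", and that route reproduces. On the likely intended reading, 90% confidence, 1300 gives about ±1 point at 5%, which is sensible for estimation. This is also a condensed article, and interval widths and design effects are often left to a fuller document.

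Most of this stands. The target has a basis, and the absence of a precision table would not by itself be a finding. The reply does not rescue the clause. The article makes a positive claim of significance level and power, and says on the strength of it that the size was calculated as sufficient. That claim is undefined as printed, wherever further detail may be kept.

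A reader might also infer that 322 families cannot supply 1300 children, because 4-6 children under 18 may include the index child and those under 2, who fall outside the 2-18 age range in Study Design and Setting. The document does not support that inference:
- It does not say whether the index child is counted. Eligibility requires a first-degree relative with T1D, who need not be a sibling.
- If one index child per family is removed, 322 × 3 to 322 × 5 is 966 to 1610. If a further 2/18 are removed as under 2 (assuming evenly spread ages), the range is 859 to 1431. Both ranges contain 1300.
- The section already provides for recruitment outside the clinic if 322 families yield fewer than 1300 children.

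**Conclusion.** The clause is wrong as written. The significance level is not a usable error rate, the power has no hypothesis to refer to, and 1300 cannot be derived from the stated inputs: the only two rates given lead to 44 or to 111 per group. About 1285 needs a margin that the document does not state, and the same margin needs about 3450 at 15%.

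It would go too far to conclude that 1300 is inadequate. The feasibility arithmetic holds, and for estimation 1300 children give 95% half-widths between about 1.2 and 1.9 points over the planning range if independent, or about 1.35 to 2.5 points under an assumed ICC of 0.1-0.2. These widths are for overall seropositivity. Widths for single stages would need an assumed stage prevalence, which the article does not give.

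The tests in the working use standard normal-approximation formulas. The margins and the ICC range are assumptions. The conclusion about the clause depends on neither.

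**What to change.** In the Sample Size section:

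1. Delete the clause on significance level and power.
2. Let the feasibility basis stand: 70% of clinic families, 322 families, about 4 children each.
3. Replace the claim of calculated sufficiency with the expected precision. For 1300 independent children, the 95% half-widths are about 1.2, 1.6 and 1.9 percentage points at 5%, 10% and 15% seropositivity. Add the widening for about 4 siblings per family, for example about 1.35-1.5 points at 5% and 2.2-2.5 at 15% under an ICC of 0.1-0.2, labelled as an assumption.
4. Optionally, state whether the 4-6 children include the index child and those under 2. No outside estimate of eligible siblings per family should be written in, since it would be a guess and the expansion provision already covers a shortfall.

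The cost is one rewritten paragraph and, once clustering is allowed for, a slightly less favourable stated precision. Enrolment does not change.
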